### Analysis of haematological and biochemical blood parameters

Qualified nurses will collect blood samples after the overnight fasting. Four vials of blood will be collected from each participant to be sure that the appropriate amount of samples will be collected: 1) 1.6 mL into a vacuum tube containing EDTA for hematologic analysis; 2) 5 mL into a vacuum tube for biochemical serum analyses run by Diagnostic Laboratory; 3 and 4) 2 vials of 5 mL into a vacuum tube for serum analyses run in the Institute of Animal Reproduction and Food Research Polish Academy of Sciences. Exhaled breath condensate samples will be collected using commercial sampling tubes (RTubes), which allow for the collection of approx. 3 mL condensate within 10 minutes. All the samples will be stored in ice and transported to the laboratories of the Institute of Animal Reproduction and Food Research of the Polish Academy of Sciences as soon as possible, where the vials with blood will be centrifuged at 3500 rpm for 10 min. The serum and condensate samples will be aliquoted and stored until analyses either in the fridge (4°C) or an ultra-freezer (-80°C), as appropriate.

In the collected samples, the following laboratory analyses will be performed to verify research hypotheses, according to the SPIRIT schedule (Fig 1):

The analysis of β-hydroxybutyric acid in serum samples (T0-T2) using commercial colourimetric assay will inform about the ketosis state in the body and adherence to the diet in the KD group.The analysis of lipid profile (total cholesterol, cholesterol HDL and LDL, triglycerides), blood morphology, and blood biochemical parameters, including liver enzymes (aspartate transglutaminase (AST), alanine transaminase (ALT), gamma-glutamyltransferase (GGT)), creatinine, uric acid, fasting glucose, insulin, haemoglobin A1c (HbA1c), C-reactive protein (CRP), albumin, total protein, ions (calcium, sodium, magnesium, potassium, phosphorus, chlorides, iron) will be performed by the Diagnostic Laboratory in Olsztyn (T0-T3) to inform about the intervention’s safety and the participants’ general body condition before, during, and after the intervention.The analysis of cytokines in serum (T0-T3) using Bio-Plex Pro™ Human Cytokine 17-plex Assay (BIO-RAD, Hercules, USA), which allows for the simultaneous analysis of Granulocyte Colony-Stimulating Factor (G-CSF), Granulocyte-Macrophage Colony-Stimulating Factor (GM-CSF), interferon-gamma (IFN-γ), Monocyte chemoattractant protein-1 (MCP-1/CCL2), Macrophage Inflammatory Protein beta (MIP-β), tumour necrosis factor-alpha (TNF-α) and interleukins: IL-1β, IL-2, IL-4, IL-5, IL-6, IL-7, IL-8, IL-10, IL-12 (p70), IL-13, IL-17A as well as the analysis of inflammation-associated parameters (lipopolysaccharide-binding protein, high sensitive-CRP) analysed using commercial ELISA kits, which will inform about the inflammatory state of the study participants.The analysis of obesity and diabetes markers in serum samples (T0-T3) using Bio-Plex Pro Human Diabetes 10-Plex Assay, which allows for the simultaneous analysis of C-peptide, ghrelin, gastric inhibitory peptide (GIP), glucagon-like peptide 1 (GLP-1), glucagon, insulin, leptin, plasminogen activation inhibitor-1 (PAI-1), resistin and visfatin. Moreover, adipsin and adiponectin concentrations in serum will be evaluated using Bio-Plex Pro Human Diabetes Adipsin and Adiponectin Assays. All these parameters will inform about the changes in the overweight-linked and metabolic functions.The analysis of Ox markers (T0-T2), including malonaldehyde, superoxide dismutase, 8-isoprostane and 8-hydroxydeoxyguanosine using ELISA kits will inform about the effect of the diet and/or loss of body weight on the Ox in the study participants.The analysis of volatile organic compounds in breath condensates (T0-T2) using solid-phase microextraction (SPME) and comprehensive two-dimensional gas chromatography with time of flight mass spectrometry (GC×GC-ToFMS) detection in breath, which will inform about the metabolic state of the study participants.The analysis of amino acids in serum samples (T0-T2) using GC-MS [48], which will inform about the nutritional state and metabolic status of the study participants.The analysis of fat-soluble vitamins (A, D, E & K) in serum samples (T0-T2) using high-performance liquid chromatography and ELISA kits as described previously [49, 50], which will inform about the nutritional state of the study participants.

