### Research objective and hypothesis

Taking into account information presented in the previous section, the proposed study was designed to evaluate the effect of KD on metabolism, inflammation, nutritional status, Ox, and obesity-associated parameters in a single, randomised and controlled study. To have better control over the diet consumed by participants, the food catering optimized by the dietician will be delivered to each person daily. To the best of our knowledge, there are no completed or ongoing studies focused on the efficiency of KD in a randomised design, with a properly balanced control group, with a homogenised diet provided to all participants during the whole intervention and analysing many parameters in a single study.

Based on current knowledge [28], and our pilot study with an animal model [43], we hypothesise that the energy-restricted KD will be more efficient in weight reduction and decreasing low-grade inflammation and oxidative stress parameters in women with overweight and obesity than a standard diet with the same calorie restriction.

This study aims to evaluate the effectiveness of an eight-week, isocaloric, energy-restricted, ketogenic diet as a weight management solution in women with overweight and obesity compared to a standard, balanced diet with the same calorie content.

The primary aim is:

to evaluate the effects of a KD on body weight and composition

The secondary aims are:

to evaluate the effect of KD-related weight loss on the inflammation and Ox in women with overweight and obesity,to evaluate the effect of KD-related weight loss on the nutritional status of the human subjects,to evaluate the effects of KD-related weight loss on the profiles of metabolites in breath, which informs about the metabolic changes in the body,to evaluate the effect of KD-related weight loss on the obesity and diabetes-associated parameters, including a lipid profile, status of adipokines, hormones,to evaluate the long-term effects and efficiency of the KD.

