### Randomization and blinding

The study participants will be randomly divided into two experimental groups. Stratified randomisation will be performed based on age and BMI. The KD group will receive a 1700 kcal ketogenic diet (fat: protein: carbohydrate ratio of 70:20:10), while the control group will receive a 1700 kcal standard balanced diet (fat: protein: carbohydrate ratio 20:30:50). Both participants and the researchers will not be blinded due to character of the intervention.

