### Statistical analysis plan

The data from this two-arm parallel randomised controlled trial is amenable to analysis using standard statistical techniques. These analyses will be undertaken using STATISTICA v. 13.3 (StatSoft, Tulsa, USA) and IBM SPSS version 28.

The primary analysis for each outcome will be by intention-to-treat, meaning that all eligible consenting participants on whom an outcome is available will be included in the analysis. All statistical tests will be two-sided. A nominal significance level of alpha = 0.05 will be used to judge significance. Where appropriate, statistical significance after controlling for the False Discovery Rate will be additionally undertaken using the Benjamini-Hochberg procedure.

For each analysis, the following summaries will be provided:

The number of participants who are included in the analysisA relevant summary measure of the outcome after an appropriate transformation (e.g., mean (SD), median (IQR) or number (%))Statistical analyses will report the effect size, 95% confidence interval and a p-value. P-values will be reported to three decimal places except where p < .001.

Analyses will be supplemented with appropriate graphical displays.

The primary outcome, weight at T2, will be compared between groups using analysis of covariance controlling for weight at T0. In general, parametric tests will be used with scale outcome data. If, for any particular analysis, there are doubts to the assuredness of validity of a parametric test then an analogous non-parametric test, will be used. ANCOVA and the non-paramteric Quade test will be used to compare randomised arms after controlling for commensurate baseline data. Simple differences between groups will be analysed using the independent sample t-test or the nonparametric Mann-Whitney test. Chemometric analyses will additionally use Principal Components Analysis (PCA), Partial Least Squares regression (PLSR) and Mutlivariable Discriminant Analysis (MDA) will be performed. The results of volatile organic compounds will be analysed using the XCMS-online platform for metabolomics. All the obtained results will be numerical and conducted in triplicates or duplicates, as appropriate.

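### Serum vitamins E and K are read as nutritional status with only the baseline value as covariate, so a lipid difference between the diets could be reported as a vitamin effect

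*Protocol article*

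**What the plan says.** In the protocol article, *Analysis of haematological and biochemical blood parameters*, the four fat-soluble vitamins are measured "in serum samples (T0-T2) using high-performance liquid chromatography and ELISA kits as described previously". The same item states what the result will mean: "which will inform about the nutritional state of the study participants". This serves a secondary aim under *Research objective and hypothesis*: "to evaluate the effect of KD-related weight loss on the nutritional status of the human subjects". The abstract adds that the trial will help close a knowledge gap on nutritional deficiencies.

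For comparisons between arms, *Statistical analysis plan* says: "ANCOVA and the non-paramteric Quade test will be used to compare randomised arms after controlling for commensurate baseline data". No lipid ratio and no concurrent lipid term is named for the vitamins.

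Under *Randomization and blinding*, one arm receives a "1700 kcal ketogenic diet (fat: protein: carbohydrate ratio of 70:20:10" and the other a "1700 kcal standard balanced diet (fat: protein: carbohydrate ratio 20:30:50". Blood lipids are measured in the same women: "The analysis of lipid profile (total cholesterol, cholesterol HDL and LDL, triglycerides" opens an item marked for T0 to T3, which covers every vitamin visit. The lipid profile is also part of another secondary aim, on "obesity and diabetes-associated parameters, including a lipid profile, status of adipokines, hormones".

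**The concern.** Vitamins E and K circulate in lipoproteins. Their serum concentration therefore tends to rise and fall with cholesterol and triglycerides even when vitamin status is unchanged. The point is limited to these two vitamins and is not made for A and D.

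Baseline adjustment removes differences between women that exist at T0. It does nothing about a lipid change that arises after randomisation and differs by arm. With fat shares of 70 and 20 at equal energy, such a difference is plausible.

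The misreading could go either way. If lipids fall more on the ketogenic diet, serum vitamins E and K could fall with them and look like a deficiency caused by the diet. If lipids rise, a true shortfall could be hidden. Either error would bear directly on the secondary aim on nutritional status.

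**Working it through.** **1. The plan's own figure.** The only sample-size figure is for weight: d = 0.5, pre-post correlation 0.7, two-sided 0.05, 80% power. The residual SD is sqrt(1 - 0.7²) = 0.714, so n = 2 × ((1.960 + 0.842) × 0.714 / 0.5)² = 32.02 per arm. This agrees with the stated 32, and 32 / 0.80 = 40 agrees with the inflated number. The article gives no variance, effect size or expected lipid shift for the vitamins, so the size of this problem cannot be derived from it. What follows is illustration.

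**2. Analytic check for vitamin E.**
- From the article: 32 per arm, two-sided 0.05, ANCOVA on the T0 value.
- Assumed: SD of log vitamin E 0.22 or 0.27; T0-T2 correlation 0.7 (the article gives 0.7 for weight only); log-log slope of vitamin E on lipids 0.6 to 1.0; lipids higher in one arm by 5 to 20%; no true difference in lipid-standardised vitamin E.
- Apparent log difference = slope × ln(1 + lipid difference).
- Standard error = SD × sqrt(1 - 0.49) × sqrt(2/32).
- Chance of significance from the noncentral t with 61 degrees of freedom.

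Worked case (SD 0.22, lipid difference 10%, slope 1.0): the log difference is ln(1.10) = 0.0953, an apparent 10%. The standard error is 0.22 × 0.714 × 0.25 = 0.0393. The noncentrality is 0.0953 / 0.0393 = 2.43, and the chance of p < 0.05 is 67%. At slope 0.6 the log difference is 0.0572 (about 6%), the noncentrality is 1.46 and the chance is 30%.

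| Lipid difference | SD 0.22, slope 0.6 to 1.0 | SD 0.27, slope 0.6 to 1.0 |
|---|---|---|
| 5% | 11-23% | 9-17% |
| 10% | 30-67% | 21-49% |
| 15% | 56-94% | 40-81% |
| 20% | 78-100% | 61-96% |

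**3. Simulation of three analyses.** 4,000 trials per setting, 32 per arm, no true change in the lipid-independent part of the vitamin. Assumed: SD of log lipids 0.18, SD of the lipid-independent part 0.20, correlation 0.7. At slope 1 the total SD is sqrt(0.18² + 0.20²) = 0.27; at slope 0.5 it is sqrt(0.09² + 0.20²) = 0.22. Entries are the percentage of trials with p < 0.05.

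| Slope | Lipid difference | Serum concentration, T0 only | Vitamin/lipid ratio | Regression adding T0 and T2 lipids |
|---|---|---|---|---|
| 1.0 | 0% | 6 | 5 | 5 |
| 1.0 | 10% | 50 | 5 | 5 |
| 1.0 | 20% | 96 | 5 | 5 |
| 0.5 | 0% | 5 | 4 | 5 |
| 0.5 | 10% | 23 | 22 | 5 |
| 0.5 | 20% | 62 | 61 | 5 |

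Two results follow. A moderate lipid difference takes the unadjusted comparison well above 5%. And the simple ratio is right only when the slope is 1: at slope 0.5 it over-corrects by as much as the serum comparison under-corrects. Regression on the lipids stays near 5% in both cases.

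**The case against.** The strongest objection is that the plan nowhere commits to unstandardised concentrations. The article cites other papers for the assays, outcomes may be summarised after a transformation, and a matching baseline value could equally be a lipid-standardised one. A separate analysis plan may settle it. This stands in part: a reader might infer that the plan has chosen raw values, and the article does not say so. But it does state what the vitamin results will mean and which covariate is used, and neither statement allows for lipids.

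A reader might also infer that the trial expects the ketogenic diet to move lipids, or to lower them. The article does not support that. Its hypothesis covers weight, inflammation and oxidative stress. The lipid reductions in the *Introduction* come from very low-calorie ketogenic diets, which the article itself says cannot be compared with a diet of this kind. The support is the contrast in fat share, which gives neither a direction nor a size.

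A third tempting inference is that the percentages above are false-positive rates of the planned test. They are not. A randomised difference in serum concentration is a valid effect of diet on serum concentration. The article sets no deficiency threshold for these vitamins, so the fault lies only in the interpretation.

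Finally, the lipid carriage of the vitamins and all vitamin-specific inputs come from outside the article, nothing was computed for vitamin K, and the false-discovery control allowed where appropriate was not modelled. All of this stands and limits how far the figures can be pressed.

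**Conclusion.** The point holds as one of interpretation. As the article stands, a difference between arms in serum vitamin E or K would be read as a difference in nutritional state, although it could arise from blood lipids alone.

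The direction and size are unknown. With 32 per arm, correlation 0.7, log-SD of 0.22 to 0.27 and slopes of 0.5 to 1.0, a 10% lipid difference would make the unadjusted vitamin E comparison significant in roughly 20-67% of trials. These inputs are assumptions. For vitamin K only the mechanism is argued.

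It would go too far to conclude that the randomised comparison is invalid, or that a vitamin-to-lipid ratio should take its place. The point concerns two of many secondary measurements. It is a cheap improvement and leaves the primary weight analysis untouched.

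**What to change.** - Keep the randomised ANCOVA on log serum concentration, adjusted for the T0 value.
- Beside it, for vitamins E and K, report a lipid-standardised comparison: preferably the same ANCOVA with log (total cholesterol plus triglycerides) at T0 and at the visit analysed as further covariates. Give the vitamin-to-lipid ratio as a sensitivity analysis.
- State in advance that a change in vitamin E or K status, or a deficiency, will be claimed only if the lipid-standardised result supports it.

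The cost is one derived lipid variable, one additional model and one sensitivity analysis per vitamin, and a few sentences in the plan. No extra sample or visit is needed. The downside is that same-visit lipids are measured after randomisation and may themselves be affected by diet. The adjusted result should therefore be labelled as an aid to interpretation and must not replace the randomised contrast.

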
**Fig 1 pone.0285283.g001:**
[figure not shown]
Content for the schedule of enrolment, interventions, and assessments according to SPIRIT requirements.

### Urine analysis

The morning urine samples will be delivered by participants. The analysis of urine including basic urine evaluation, creatinine, uric acid, and ions (Ca, Na, Mg, K, P, Cl) will be performed by the Diagnostic Laboratory in Olsztyn (T0-T3). The analysis of the amino acid profile in urine (T0-T2) will be performed by the same method as in serum.

### Diet control

The diet will be provided daily to each participant to maintain homogeneity and to reduce the risk of drop-out caused by a lack of wish to prepare meals. Each participant will receive a study diary to record any possible side effects. All received and consumed meals from the catering and, if any, intake of the products not from the catering will have to be marked in the diary to evaluate diet compliance.

To evaluate the diet followed by the participants before and after the nutritional intervention, food frequency questionnaire-6 (FFQ-6) [51] will be applied for a retrospective semi-qualitative food intake evaluation at T0 and T3. The FFQ is well-validated and recognised as universal and independent of the geographic and subjective tools for researching eating patterns. It is also the most commonly used instrument to assess past dietary intake in epidemiological studies on the relationship between dietary factors and diseases, primarily because of its low cost and ability to capture usual dietary patterns [52]. Frequency data can explain much of the variation in dietary intake, and FFQs can provide sufficient accuracy to rank individuals in terms of risks for subsequent health outcomes. FFQs have been used in many studies to predict associations between dietary intake and disease-specific mortality and morbidity [53, 54]. The FFQ Food Consumption Frequency Questionnaire is a qualitative questionnaire, but it is also a good tool for semi-qualitative research when combined with a diary. It is a tool for collecting information on the frequency of consuming 62 assortment groups of products, representing 8 main groups of food consumed in the last 12 months. The respondents can choose from (6–10) categories of food consumption frequency: from minimal (1) never or almost never to maximal (6/10) several times per day.

### Quality of life

At the T0, T2 and T3 visits, Quality of Life (QoL) questionnaires will be completed by participants to evaluate the effect of diet and/or weight loss on the quality of life. The health-related quality of life questionnaire (HRQoL) is a suitable tool for randomised controlled trials as well as observational studies. HRQoL was introduced by CDC in 2000 [55]. The HRQoL combines three separate modules to assess perceptions of HRQoL. It is widely used by health professionals and was designed to bridge the gap between disciplines, such as sociology, psychology, and economics, about the drivers of QoL. It is for this reason that the questionnaire is fairly broad in its focus. It is available in text or graphic versions. The scale of responses ranged from 1 (excellent) to 5 (poor).

### Statistical analysis plan

The data from this two-arm parallel randomised controlled trial is amenable to analysis using standard statistical techniques. These analyses will be undertaken using STATISTICA v. 13.3 (StatSoft, Tulsa, USA) and IBM SPSS version 28.

The primary analysis for each outcome will be by intention-to-treat, meaning that all eligible consenting participants on whom an outcome is available will be included in the analysis. All statistical tests will be two-sided. A nominal significance level of alpha = 0.05 will be used to judge significance. Where appropriate, statistical significance after controlling for the False Discovery Rate will be additionally undertaken using the Benjamini-Hochberg procedure.

For each analysis, the following summaries will be provided:

The number of participants who are included in the analysisA relevant summary measure of the outcome after an appropriate transformation (e.g., mean (SD), median (IQR) or number (%))Statistical analyses will report the effect size, 95% confidence interval and a p-value. P-values will be reported to three decimal places except where p < .001.

Analyses will be supplemented with appropriate graphical displays.

The primary outcome, weight at T2, will be compared between groups using analysis of covariance controlling for weight at T0. In general, parametric tests will be used with scale outcome data. If, for any particular analysis, there are doubts to the assuredness of validity of a parametric test then an analogous non-parametric test, will be used. ANCOVA and the non-paramteric Quade test will be used to compare randomised arms after controlling for commensurate baseline data. Simple differences between groups will be analysed using the independent sample t-test or the nonparametric Mann-Whitney test. Chemometric analyses will additionally use Principal Components Analysis (PCA), Partial Least Squares regression (PLSR) and Mutlivariable Discriminant Analysis (MDA) will be performed. The results of volatile organic compounds will be analysed using the XCMS-online platform for metabolomics. All the obtained results will be numerical and conducted in triplicates or duplicates, as appropriate.

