### Sample size

On trial opening, the first 80 women meeting eligibility criteria who also do not meet any of the exclusion criteria will be selected. The focus on only female subjects was based on eliminating biological sex as a factor that could affect the results. Moreover, it is scientifically proven that women have better trust in healthy nutrition and more engagement and compliance in dietary programs [46, 47], thus a lower number of drop-outs is expected. At the end of the intervention, dietary efficacy is projected to be between the equivalent of one dress size to one and a half dress sizes, equating to a weight loss of approximately 5kg. For BMI between 28 and 35, the standard deviation of weight is approximately 5kg equating to an intra-group standardised effect of 1. However, a downward revision in standardised effect size for a between groups comparions for an intent-to-treat analysis Analysis of Covariance (ANCOVA) would indicate that n = 32 women per group would have at least 80% power to detect a standardised difference of Cohen’s d = 0.5 (alpha = 0.05, two-sided) assuming a pre- post- correlation in weight of 0.7. Inflation of sample sizes to account for loss to follow-up would indicate n = 40 per group would provide a safety margin for a comparison between group means. This sample size is conservatively consistent with Mohorko et al. [39]. The sample size will support within-groups, between-groups, and whole-group analyses for the secondary research questions.

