### Sample collection

There will be 3 sample collection points for each participant during the nutritional intervention: at baseline (T0), after four weeks (T1) and after eight weeks (T2). Because of the relatively high number of participants, to avoid long queues and irritation of participants, the check-up visits will be divided into four days a week. Check-up visits will be carried out in the Pantamed Primary Care Unit under the medical doctor’s supervision and qualified nurses. Moreover, after one year (T3), the check-up visit is planned to evaluate the regain of body weight, the nutritional habits, and the potential long-term effects of this intervention, focusing on obesity, diabetes, and low-grade inflammation-associated parameters.

During each check-up visit (T0-T3), in the overnight-fasting participants, height, body weight, body composition, as well as the waist and hips circumference will be measured, the check-up made by the medical doctor, including systolic, diastolic and pulse pressure, will be performed and the samples will be collected. BMI will be calculated based on body mass [kg] divided by the square of body height [m] and expressed in kg/m^2^. The body weight and composition will be measured using TANITA Body Composition Analyser, while the waist circumference will be measured using a standard measurement tape.

The participants who will not follow the diet for more than 80% of the trial period or will initiate the pharmacological therapy prescribed by the physician during the intervention will be eliminated from the study.

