### Potential risks

The potential risk can be the collection of a too-low volume of blood and breath condensate. To overcome this risk, qualified and experienced nurses will be involved in the sample collection. Another risk is the problem with recruitment. To encourage participants to take part in this study, the local media will be involved to the extent allowing fulfilling the sample size. The recruitment will be initiated sufficiently earlier to collect 80 participants. The potential problem is the drop-out in the long-term data. To overcome this issue, in case of moving participants to other cities or countries, different contact data (e-mail address, phone numbers) will be collected to arrange the follow-up meeting at a suitable time for the participant.

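### The primary analysis called intention-to-treat is complete-case at T2 and leaves unused the week-4 weight of women who drop out, so the arm difference is biased if response-related drop-out differs between arms

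*Protocol article*

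**What the plan says.** The Statistical analysis plan section states "The primary analysis for each outcome will be by intention-to-treat", and explains this to mean that "all eligible consenting participants on whom an outcome is available will be included in the analysis". It then fixes the main model: "The primary outcome, weight at T2, will be compared between groups using analysis of covariance controlling for weight at T0".

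The Sample collection section provides for weight at every visit: "During each check-up visit (T0-T3), in the overnight-fasting participants, height, body weight, body composition". T1 falls at week 4 and T2 at week 8. A later visit is also planned: "after one year (T3), the check-up visit is planned to evaluate the regain of body weight".

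Loss is foreseen. In Sample size, "Inflation of sample sizes to account for loss to follow-up would indicate n = 40 per group", up from 32. In Potential risks, "The potential problem is the drop-out in the long-term data"; the remedy offered there is to collect more contact details. Randomization and blinding says that neither participants nor researchers are blinded.

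**The concern.** The analysis set and the model together decide what happens to a woman without a T2 weight: she does not count. That is an available-case set under the intention-to-treat label. It is a rule the document states, not a detail it leaves open.

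If she attended at week 4, her T1 weight is on file. It is likely to predict both whether she left and what she would have weighed at week 8. The primary model uses only T0, so it cannot correct for drop-out that follows early success or failure. In an open-label diet trial such drop-out is plausible, and it may not be alike in the two arms. Raising 32 to 40 per group protects power but does nothing about this bias.

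**Working it through.** **1. The plan's own figures.** Inputs from Sample size: d = 0.5, SD 5 kg, pre-post correlation r = 0.7, two-sided alpha 0.05, 80% power.

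- n per group = 2(1 − r²)(z₀.₉₇₅ + z₀.₈₀)²/d² = 2 × 0.51 × (1.960 + 0.842)²/0.25 = 32.02, which agrees with the stated 32.
- 32/(1 − 0.20) = 40, so the inflation implies a 20% loss.
- Target difference = 0.5 × 5 kg = 2.5 kg.
- ANCOVA standard error with 32 per arm analysed = 5 × √0.51 × √(2/32) = 0.89 kg.

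The sample size is not in dispute.

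**2. Assumptions the document does not give.** T0–T1 and T1–T2 correlations of 0.85/0.85, 0.80/0.90 or 0.90/0.80; drop-out of 10% to 30% per arm; log-odds of drop-out rising by 0.5 or 1 per SD of poorer T0-to-T1 weight change, or not at all (0). Every woman is assumed to have a T1 weight.

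**3. Simulation.** 500,000 women per arm, no true difference, SD 5 kg and T0–T2 correlation 0.7. The table gives the bias in kg of the complete-case ANCOVA of T2 on T0, in favour of arm A. A and B are labels only, since the direction is not known.

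| Drop-out, A v B | Log-odds per SD, A v B | 0.85/0.85 | 0.80/0.90 | 0.90/0.80 |
|---|---|---|---|---|
| 20% v 20% | 1 v 1 | 0.00 | 0.01 | 0.00 |
| 20% v 20% | 0.5 v 0 | 0.23 | 0.26 | 0.18 |
| 20% v 20% | 1 v 0 | 0.41 | 0.47 | 0.33 |
| 30% v 10% | 0.5 v 0.5 | 0.22 | 0.25 | 0.18 |
| 30% v 10% | 1 v 1 | 0.38 | 0.44 | 0.31 |
| 30% v 10% | 1 v 0 | 0.59 | 0.68 | 0.48 |

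So the bias is about 0.2 to 0.7 kg when the pattern differs between arms and about 0 when it is the same. An extreme case, in which exactly the poorest early responders leave (30% v 10%), gives 0.59 to 0.84 kg. I treat that as an outer bound.

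**4. The same data using T1.** Missing T2 weights were predicted from T0 and T1 within arm, and the ANCOVA was then run on all women. The result was within about 0.01 kg of the full-data result in every row.

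**5. Against the plan's scale.** 0.2/2.5 = 8% and 0.7/2.5 = 28% of the target. With a standard error of 0.89 kg, a bias of 0.2 kg raises the two-sided type I error from 5% to about 5.6%, 0.5 kg to about 8.7%, and 0.7 kg to about 12.3%.

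**6. Limit of the remedy.** If half of the drop-outs have no T1 weight, the 20% v 20%, 1 v 0 pattern leaves 0.15 to 0.21 kg of the 0.33 to 0.47 kg bias.

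**The case against.** The strongest reply is that this is a journal article, and that imputation and sensitivity analyses are commonly left to an analysis plan that is not shown. That stands for those items, and their absence is not the point here. It does not cover the primary set and model, which the article fixes.

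The reply also limits what may be inferred:

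- A reader might infer that the document expects the ketogenic arm to lose more women. The Introduction says only that a restrictive diet could raise drop-out over longer intervals, mainly with extreme calorie reduction. Here both arms receive 1700 kcal with meals delivered for eight weeks. The Discussion cites some evidence of faster early loss on the ketogenic diet, which could instead put response-driven drop-out in the control arm.
- A reader might infer that more than 20% loss is expected at one year. Potential risks names a possible problem and gives no rate.
- A reader might say the ANCOVA is valid only if missingness is unrelated to response. For the arm contrast that is too strong, as the first row of the table shows.
- A reader might take it as settled that earlier weights go unused at T3. The definition of the analysis set covers every outcome, but no specific model for T3 weight is given.

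Finally, the near-zero bias with T1 follows partly from construction, because simulated drop-out depends only on an observed T1. The article expects early side effects of ketosis in the first few days, so some women may leave before week 4.

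**Conclusion.** The point holds in conditional form. The primary analysis is complete-case at T2, carries the intention-to-treat label, and does not use the T1 weight of women who leave between weeks 4 and 8. If response-related drop-out differs between arms, the estimated difference is biased by about 0.2 to 0.7 kg, in a direction the document does not settle. That compares with a 2.5 kg target and a standard error of about 0.89 kg. If drop-out is alike in both arms, the bias is about zero.

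The SD and the T0–T2 correlation are the document's; the T1 correlations and drop-out patterns are assumptions. Confidence is high on what the plan fixes, and lower on the size of the bias. This is a worthwhile and cheap improvement, not a flaw that invalidates the trial.

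**What to change.** - Define the primary analysis set as all randomised women.
- Estimate the T2 arm difference from a likelihood-based repeated-measures model of the T1 and T2 weights, with arm, visit, arm-by-visit, T0 weight and T0-by-visit, adjusted for the stratification factors (age and BMI), with unstructured covariance.
- Keep the T2 ANCOVA on observed cases as a sensitivity analysis.
- Analyse T3 weight as a secondary outcome in the same way, in a separate model that also uses the T1 and T2 weights, so that the eight-week result does not depend on one-year data. Add one sensitivity analysis that departs from missing at random, for example assuming that missing women are back at their T0 weight.

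The cost is a change of wording and modest analysis work. No new visits or measurements are needed, and SPSS, which the plan names, fits such a model. The downside is that the result rests on a missing-at-random assumption, and women lost before T1 gain little from the model. The number lost before T1 should therefore be reported by arm.
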